## Abstract

**Background:**

The aim of the study is to reduce the high prevalence of tooth decay in children in a remote, rural Indigenous community in Australia, by application of a single annual dental preventive intervention. The study seeks to (1) assess the effectiveness of an annual oral health preventive intervention in slowing the incidence of dental caries in children in this community, (2) identify the mediating role of known risk factors for dental caries and (3) assess the cost-effectiveness and cost-benefit of the intervention.

**Methods/design:**

The intervention is novel in that most dental preventive interventions require regular re-application, which is not possible in resource constrained communities. While tooth decay is preventable, self-care and healthy habits are lacking in these communities, placing more emphasis on health services to deliver an effective dental preventive intervention. Importantly, the study will assess cost-benefit and cost-effectiveness for broader implementation across similar communities in Australia and internationally.

**Discussion:**

There is an urgent need to reduce the burden of dental decay in these communities, by implementing effective, cost-effective, feasible and sustainable dental prevention programs. Expected outcomes of this study include improved oral and general health of children within the community; an understanding of the costs associated with the intervention provided, and its comparison with the costs of allowing new lesions to develop, with associated treatment costs. Findings should be generalisable to similar communities around the world.

The research is registered with the Australian New Zealand Clinical Trials Registry (ANZCTR), registration number ACTRN12615000693527; date of registration: 3rd July 2015.

## Background

Globally, of the 50 most prevalent chronic diseases, four are related to oral health: (1) dental caries of permanent teeth, (2) chronic periodontitis, (3) dental caries of deciduous teeth and (4) edentulousness (total tooth loss) [1, 2]. Tooth loss is predominantly a consequence of dental caries in the permanent dentition and adult chronic periodontitis, and potentially results in substantial social and health consequences. Dental caries in the deciduous dentition is a significant predictor of dental caries in the permanent dentition [3]. With few exceptions, both dental caries and periodontitis are preventable conditions with adequate self-care and healthy lifestyle habits, with additional health promotion and preventive interventions at the health services level [4, 5]. However we continue to struggle to significantly reduce, and preferably eradicate, the burden of preventable oral health conditions. Appropriate self-care is largely dependent on the social and health capital of the community [6]. In disadvantaged, marginalised, rural and Indigenous communities, this is often absent. These communities also have the additional burden of limited health promotion and preventive services, carry a significant health burden and suffer a seriously reduced oral health-related, and overall quality of life [7, 8].

Most dental health promotion and preventive services require professionally trained personnel, needing equipment and regular availability of the service for the re-application of interventions. The current evidence is that a number of dental preventive interventions require re-application 2 to 4 times a year [9, 10]; and in disadvantaged and especially remote communities, this is usually not possible, and the burden of the common oral diseases is never dealt with: more importantly, never prevented. To our knowledge there is currently no evidence on the effectiveness, cost-effectiveness and cost-benefit of a less frequent and therefore sustainable dental preventive intervention strategy.

The proposed study will implement a novel dental caries preventive intervention in children to firstly reduce the pathologic bacterial load using an oral anti-septic, secondly seal the part of the tooth most prone to decay with a fissure sealant, and thirdly to strengthen the tooth structure with a fluoride varnish, all during a single annual visit, in a rural remote Indigenous community in Far North Queensland, Australia. While there are data on the effectiveness of the three specific interventions, we have developed a novel approach to assess a less frequent combined application of these interventions. Importantly, we will assess its effectiveness and its cost effectiveness to determine the value for money of the service.

The team believes that the current suggested frequency 2–4 times per year for these preventive interventions is not possible, or sustainable, in poorly-resourced, remote communities and is proposing an alternative strategy requiring fewer resources to address the burden of dental decay in children.

### Burden of dental caries in Indigenous communities in Australia

In Australia, dental conditions are especially prevalent in Indigenous communities, and are a significant health burden in rural remote communities [7, 8]. A recent report of the dental caries status of Indigenous children in Australia showed that those located in rural and/or remote areas have a much higher mean number of decayed, missing and filled deciduous teeth (dmft) (~4 in 6-year old children) compared to non-Indigenous children in metropolitan (dmft ~ 1.5) and rural settings (dmft ~ 1.8) as well as Indigenous metropolitan children (dmft ~ 2.6) [11]. The situation is similar in the permanent dentition of older children. The National Survey of Adult Oral Health found that 57 % of Indigenous adults had untreated coronal dental caries, compared with 25 % of non-Indigenous adults [12]. The mean number of decayed teeth amongst Indigenous adults (>15 years of age) was 2.7 compared to 0.8 amongst non-Indigenous adults.

There are high social costs associated with poor dentition, and a diminished quality of life due to pain and discomfort [13–16], and especially because of long waiting lists for treatment [17]. Social costs include lack of sleep, lost time for school, behavioural problems, lack of cooperation and diminished learning. Lost working time for parents accompanying children to dental treatment sessions has been reported to lead to a loss of employment. Studies in this area need to appreciate the full impact of childhood caries on the child, family and society.

An oral health survey in 2004 (pre-water fluoridation) in the Northern Peninsula Area (NPA) of far north QLD, found that dental caries experience of 6- and 12-year-old children was more than twice that of the state average and more than four times greater than the comparable figures for Australian children overall. Soon after this survey the reticulated water supply of the five small rural communities in this area was fluoridated. A follow-up oral health survey in NPA conducted in November 2012 by this team, in which we examined over 70 % of known resident schoolchildren (*n* = 339), suggests that the dental caries status has improved significantly since the 2004 survey [18]. Few teeth had restorations in both surveys. Age-weighted overall caries prevalence and severity declined from 2004 to 2012 by 37.3 %. The effect was most marked in younger children, dmft decreasing by approximately 50 % for ages 4 to 9 years; at age six, mean decayed score decreased from 5.20 to 3.43. DMFT levels decreased by half in 6 to 9 year old children. However, significant unmet treatment needs exist at all ages. To address this, practical and affordable ways have to be found.

One of the reasons for the improved oral health status could be due to fluoridation of the local water supplies. Whilst the economic viability of water fluoridation for a small community such as this might be questioned, we posit the costs are outweighed by the significant caries reduction in both the deciduous and permanent dentitions as found in our study [18]. Moreover, the fluoridation plant has functioned erratically since being implemented and has been out of operation since April 2011 following a lightning strike. The likelihood that the water will again be fluoridated is uncertain due to budget constraints and because the 2012–2015 Queensland State Government legislated to give local governments across the State the power to decide to fluoridate or not. Dental caries rates may again increase in the absence of water fluoridation. It will be crucial to investigate alternative models to ensure improvements in dental caries incidence in this resource-constrained community. The envisaged dental prevention model will essentially reduce the microbial load with the topical disinfectant, povidone iodine [10]; inhibit biofilm adherence to susceptible sites by application of fissure sealants [19] and reduce the susceptibility of the tooth to demineralisation by acids generated in the microbial biofilm by the application of a fluoride varnish [9, 20]. Measures of local fluoride concentration [20] and of oral mutans streptococci counts return to baseline after a few months [21], so that most reported studies have used regular re-applications (2–4 times per annum), which would be difficult to implement in remote settings lacking appropriately trained personnel and resources. Fissure sealants, on the other hand, have excellent longevity [19].

To date, the reported economic burden of childhood caries is likely to be underestimated, as previous reports did not capture the full scope of costs and missed the potential cost-savings of prevention programs. There are few studies involving child populations that evaluate the cost-effectiveness of prevention programs for childhood caries [22]. Savage et al. [23] concluded that pre-school aged children in the USA who had early dental prevention visits would experience lower dental-related costs over 5 years. Similarly, a second USA study by Ramoz-Gomez et al. [24] looked at minimal, intermediate and comprehensive prevention programs and concluded that all three were cost-effective. They concluded that government health systems can save considerable resources by investing in early childhood caries prevention. A study by Lee et al. [25] in Carolina, USA, found early dental visits were highly cost-effective for high-risk children. These studies reiterate the need for translating this evidence into policies for childhood caries prevention. Although the cost-savings of prevention programs are based on predictions, the potential economic benefits are encouraging.

### Review of interventions to reduce the incidence of dental caries in children

#### Pit and fissure sealants

Dental decay most often occurs on the occlusal pits and fissures of permanent molar teeth. A pit and fissure sealant is defined as a material [both glass-ionomer and resin-based materials are widely used] that is introduced into the occlusal pits and fissures of caries susceptible teeth [19]. Its application to newly-erupted posterior teeth is the best method to prevent pit and fissure caries, and/or to prevent the continued development of incipient caries into frank caries when the incipient lesion is sealed over. Sealing the occlusal surfaces of permanent molars in children and adolescents reduces the incidence of new carious lesions for up to 48 months when compared to no sealant. Recommendations and reviews of the evidence of preventing dental caries through school-based sealant programs suggest that it remains an important and effective public health approach [26].

#### Fluoride varnish

Fluoride varnishes are a liquid resin or synthetic base that contain a high concentration of fluoride and set quickly on contact with teeth, even in the presence of saliva [9]. Fluoride ions in the material are released when the pH drops in response to acid production in the biofilm on the tooth surface and these become available to promote remineralisation of damaged tooth enamel in early carious lesions (white spots). The fluorhydroxyapatite formed over time during the remineralisation process in an initial caries lesion is more resistant to future demineralisation. Children at moderate or high-risk to dental caries benefit from fluoride varnish programs. Varnish delivers a higher concentration of fluoride than other professionally applied fluoride gels and foams; therefore it is applied in smaller amounts.

The fluoride varnish layer slowly disappears over time and needs repeated application to maintain effectiveness as a primary prevention strategy. While one application of fluoride varnish may provide some benefit, the majority of studies of professionally applied fluoride demonstrate that at least two applications each year, for at least 2 years, are necessary to demonstrate effective reductions in dental caries, making this a difficult strategy in disadvantaged communities who are most in need of this intervention [20].

#### Povidone (PVP)-iodine addition to fluoride

Children with high rates of tooth decay are much more heavily colonized with pathogenic bacteria than children who experience less tooth decay [27]. PVP-iodine interferes with the ability of *mutans streptococci* to bind to tooth surfaces by disrupting the expression and production of glucosyltransferase [28]. A seminal in vitro study of anti-plaque agents demonstrated that 1 % iodine (10 % PVP-iodine is 1 % active iodine) was bactericidal to intact *S. mutans* biofilm [29]. A series of studies have led scientists to conclude PVP-iodine is an appropriate adjunctive antimicrobial for use on teeth to prevent tooth decay [10, 21, 30, 31].

Topical Treatment by PVP-Iodine in conjunction with Fluoride Varnish is simple [32]. The iodine comes in a single application swab. The total treatment time is 3 to 4 min and costs less than 20 cents. Clinically the teeth are brushed to remove debris and disrupt the biofilm; then dried with gauze, and painted with 0.2 ml PVP-Iodine. After the iodine application, the teeth are dried again and coated with fluoride varnish at the same visit.

As a result of our recently conducted oral health survey in the NPA, the research team has established networks and support from the local community, health workers and schools, as well as from Queensland Health (QH), the State agency responsible for all public health services. The importance of sustainable dental prevention interventions is evident, especially if fluoridation of the water supplies is not to continue. This study will assess the effectiveness, cost-effectiveness and benefits of a novel single annual dental caries preventive intervention in a remote rural Indigenous community in north Queensland.

### Aims and hypotheses

The study seeks to (1) assess the effectiveness of an annual oral health preventive intervention in slowing the incidence of dental caries in children in a remote, rural Indigenous setting, (2) identify the mediating role of known risk factors for dental caries and (3) assess the cost-effectiveness and cost-benefit of the intervention.

We hypothesise that 1 and 2 years after the intervention (1) the actual incidence of dental caries in children will be significantly lower than the expected incidence, based on modelling from the two oral health surveys conducted over the past 11 years in the same community, the current survey and (2) the intervention will be cost-effective and cost beneficial, and therefore feasible and sustainable for broader implementation across similar communities in Australia and internationally.

## Methods

### Study design

This is a longitudinal preventive intervention study. All school children in the NPA will be invited to participate. As it is unethical to withhold any proven intervention from any child, no control group will be created. Children who do not consent to participate may be natural controls if they consent to a dental examination at the end of the study. The actual caries increment in the children who participate will be compared to the expected caries increment modelled on oral health surveys carried out in this community in 2004 (pre-water fluoridation); in 2012 (by the Griffith University team post-partial water fluoridation) and 2015 (baseline survey for this study).

All consenting children will undergo a detailed head, neck and dental clinical examination and complete a questionnaire on their basic demography (gender and age), residential history (exposure to fluoridated drinking water), own general and oral health perceptions; oral health behaviours, attitudes and knowledge; dental visits; diet and oral health-related quality of life.

All active disease will be treated prior to implementing the dental caries preventive intervention. In years 2 and 3 of the study, all participating children will be invited to return for a dental examination, treatment of new incident disease and repeat of the prevention regime.

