### Analysis

All baseline socio-demographic characteristics will be described for the selected sample using counts and frequencies. Baseline and follow-up caries experience and questionnaire related information will be reported. Dental caries increment (incidence) will be the main outcome measure used to determine the effectiveness of the preventive intervention. The expected caries increment will be modelled from the three oral health surveys conducted in this community (2004; 2012 and 2015) and compared with the actual caries increment from 2015–2016; 2016–2017 and 2015–2017. The mean caries increment will be compared between the expected (modelled) and actual findings, and adjusted for known risk factors for dental caries. The hypothesis will be that caries increment observed in the period of 2015 to 2017 is smaller than the modelled caries increments. Two independent samples *t*-test will be used for the analysis with significance being determined if *p* < 0.05.

Children who receive only a part of the intervention will be separately assessed: for example we will have children who fully participate, those with baseline and only a year 1 follow-up, those with baseline and only a year 2 follow-up. This will ‘naturally’ further inform us on the most appropriate frequency of this preventive strategy. Both a group and matched analysis will be conducted to account for children who receive only part of the intervention.

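### The modelled increment that replaces a control group is tested by a t-test that carries no forecast error, and no check of it on 2012–2015 is described

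*Protocol article*

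**What the plan says.** Study design in the protocol article states that "no control group will be created". The comparator is a modelled one: "The actual caries increment in the children who participate will be compared to the expected caries increment modelled on oral health surveys carried out" in 2004 (before fluoridation), in 2012 (after partial fluoridation) and in "2015 (baseline survey for this study").

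Analysis repeats this: "The expected caries increment will be modelled from the three oral health surveys conducted in this community (2004; 2012 and 2015"). It then says "The mean caries increment will be compared between the expected (modelled) and actual findings, and adjusted for known risk factors for dental caries". The test is a two-independent-samples t-test at p < 0.05, with sidedness not stated. Hypothesis 1, under Aims and hypotheses, is that "the actual incidence of dental caries in children will be significantly lower than the expected incidence".

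One other untreated group is mentioned, conditionally: "Children who do not consent to participate may be natural controls if they consent to a dental examination at the end of the study".

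Transition probabilities takes the non-intervention rates of the Markov model from the same modelled data.

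**The concern.** The effect estimate is the actual increment minus a forecast. If the forecast is too high, the trial shows a benefit that is not there. If it is too low, a real benefit is masked. A two-sample t-test measures variation between children. It has no term for the possibility that the model itself is off, and examining more children does not shrink that error.

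The background makes the forecast hard to trust without a check. Under Burden of dental caries in Indigenous communities in Australia, "at age six, mean decayed score decreased from 5.20 to 3.43" between 2004 and 2012. The same section reports that the fluoridation plant ran erratically, has been out of operation since April 2011, and that caries may increase again without it. The article therefore supports a continued fall, a plateau or a rebound, and does not say which the model assumes.

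Both the effectiveness claim and the cost-effectiveness result, which are meant to inform wider implementation, rest on this one forecast.

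**Working it through.** The article gives no sample size, power or effect size, so there is no figure of its own to reproduce. Three checks follow.

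**1. Does any other comparator supply an increment?** Non-consenting children may be examined at the end only. With no planned baseline they yield no increment, and Analysis plans no comparison using them. Partial participants differ in how much of the intervention they received; they are not untreated. For the primary increment the forecast is in effect the sole comparator.

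**2. How far do simple forecasts differ?** Inputs: age-six mean decayed score 5.20 (2004) and 3.43 (2012).
- Linear slope: (3.43 − 5.20)/8 = −0.221 per year.
- Constant yearly ratio: (3.43/5.20)^(1/8) = 0.949.
- Rebound: +0.221 per year from 2012.

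| Form | 2015 | 2017 |
|---|---|---|
| Linear | 2.77 | 2.32 |
| Constant ratio | 2.93 | 2.64 |
| Flat | 3.43 | 3.43 |
| Rebound | 4.09 | 4.54 |

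The 2017 values span 4.54 − 2.32 = 2.2 teeth. These are levels at one age, not increments, and they leave out the 2015 survey. They show that two survey points do not settle the form, and that the 2015 baseline could help to tell these forms apart.

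**3. What does forecast error do to the planned test?** Assumptions not in the article: SD of the increment 2 teeth; 339 per side (the size of the 2012 survey, not of this trial); two-sided 0.05; no true effect.
- SE = 2 × √(2/339) = 0.154 teeth.
- With the forecast too high by b, the chance of a favourable p < 0.05 is Φ(b/SE − 1.96).
- b = 0: Φ(−1.96) = 2.5%.
- b = 0.24: about 34% (23% at SD 2.5, 54% at SD 1.5).
- b = 0.30: Φ(1.95 − 1.96) = 50% (17% to 93% over n 200–600 and SD 1.5–3).

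The value 0.24 comes from one simple case. Suppose 2015 equals 2012 and the three surveys are averaged equally: (5.20 + 3.43 + 3.43)/3 = 4.02, and 4.02/3.43 = 1.172, or 17% too high. A two-year increment of 3.43 × 2/5 = 1.37 teeth (assuming even accrual over five years) then gives 0.172 × 1.37 = 0.24.

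If the forecast error is instead random with an assumed SD τ = 0.3 teeth and is left out of the SE, the true two-sided error rate is 2 × [1 − Φ(1.96 × 0.154/√(0.154² + 0.3²))] = 37%. Including it raises the SE to √(0.154² + 0.3²) = 0.337, and the difference needed for significance from 1.96 × 0.154 = 0.30 to 1.96 × 0.337 = 0.66 teeth.

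**The case against.** The strongest reply is that much of this is silence in a condensed article. Model specification, validation and a lock date commonly sit in a full protocol or analysis plan, which is not shown. A reader might infer that the model will be settled only after the 2016 and 2017 results are known, or that using 2015 in the fit rules out testing the forecast. The article supports neither. All three surveys precede follow-up, so the model can be fixed in time, and a final three-survey fit does not prevent an earlier back-test on two. Those readings are not part of this point. What stands is the stated analysis: a forecast as comparator, tested as though it were a second sample.

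The article also plans adjustment for risk factors and records exposure to fluoridated water. Both may improve the forecast, but neither puts its error into the test. Probabilistic sensitivity analysis is planned for the cost model. That helps only if the distributions for the non-intervention rates are wide enough to include forecast error.

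The back-test is imperfect. Fluoridation changed between surveys, so a miss in 2015 would mix model error with changed exposure. It would also compare survey levels three years apart, not within-child increments. This limits what it proves but leaves it informative: the plant was already off before the 2012 survey, as it is reported to be when the trial starts.

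Finally, the percentages in the working do not describe the planned model, whose form is not given. This is correct, and they are offered only as illustration.

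**Conclusion.** The point holds as a weakness in the stated analysis, and the plan should change. The forecast is the effective sole comparator for the primary increment, its error enters the estimated effect one for one, the planned t-test does not carry that error, and no check on 2012–2015 is described. Forecast error could therefore be reported as an effect or conceal one, and it would also carry into the cost-effectiveness result.

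On size, overshoots of 0.24 to 0.30 teeth are enough to turn a 2.5% chance of a false favourable result into roughly 34% to 50%. This rests on an assumed SD of 2, 339 per side and, for the lower value, assumed weighting and accrual. It shows that modest bias matters; it does not estimate this trial's error rate. Nor do the documents show that the forecast will be too high rather than too low.

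**What to change.** Before the 2016 data are seen:

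1. Fit the model on 2004 and 2012 only, predict the 2015 baseline by age, and report forecast minus observed, interpreted in light of the change in fluoridation.
2. Refit with 2015, then fix the model and each child's expected 2015–2016 and 2015–2017 increments, with a date.
3. Replace the plain two-sample t-test with a comparison of actual against the fixed expectation whose interval includes forecast uncertainty, informed by step 1. Show the result under the other plausible forecasts (flat, trend, rebound), and carry the same uncertainty into the non-intervention rates of the Markov model.

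The single back-test error should not serve as a pass mark for claiming an effect: it could be near zero by chance, or large because of fluoridation. The article should also say that the possible natural controls, examined only at the end, cannot supply an increment.

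Cost: a few days of analysis on the two earlier surveys and the baseline, with no added visits. The interval will be wider, so the effectiveness claim will be more cautious.
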